### **Statistical Analysis Plan**

All analyses will be carried out using SAS System 9.4 for Windows. Statistical tests will be 2 sided, with confidence levels of 0.05. Prior to testing, a series of univariate analyses will be carried out to ensure that model assumptions are met. To address the primary study hypothesis, a mixed-effect model will be used to account for the longitudinal nature of the data, and for attrition. Missing values will be treated with maximum likelihood estimation in SAS PROC MIXED, which uses all available information in the data. Intention-to-treat analysis will be used; all participants will be analyzed as they were originally allocated after randomization. As a sensitivity analysis, the final model will be fitted only with subjects for whom there is complete data. Formal help-seeking score will be the dependent variable, with study groups (intervention and control) and time points as predictors, and relevant socio-demographics collected at baseline as covariates to control for possible confounding.

The interaction between study group and time will be included in the model, and linear contrasts will be used to compare the groups, specifically regarding the change from baseline to the final time point. Similar models will be used to address the exploratory hypotheses, which examine different scales and trends, on the effect of the intervention over time. Bonferroni adjustment will be used to control the Type I error rate if multiple comparisons are desired. Generalized estimating equations will be used for the AHSQ, since this scale is binary.

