Our target population for this study is transition aged youth in post-secondary settings. Throughout this document we refer to them as students, participants, and/or youth. To take part in the study, participants must be transition-aged youth [19] of any gender who are currently enrolled in part-time or full-time studies at one of 3 participating postsecondary institutions in the GTA: University of Toronto, Ryerson University, and George Brown College. At baseline, 236 subjects will be recruited for the intervention arm and 236 subjects for the control arm, which amounts to 472 subjects in total. Participants will be compensated for their time. Data will be collected at baseline, 3 and 6 months from all participants through a battery of online questionnaires to measure primary outcomes (changes in help-seeking intentions), help-seeking behaviours and help-seeking attitudes (secondary outcomes) as well as self-reported changes in self-stigma and self-efficacy, data on demographics and general mental health status. The duration of the study is 6 months.

Participants in the intervention arm will additionally complete a usability survey at the 6-month mark to measure usefulness, satisfaction and ease of use of the Thought Spot application. The purpose of the survey is to explore factors related to app acceptance, feasibility and performance that may affect help-seeking intentions, behaviours and attitudes. Based on the usability survey results, a purposeful sample of 15-20 participants who completed this survey will be invited to participate in a 30-minute qualitative interview to better understand enablers and barriers to using Thought Spot and its impact on help-seeking intentions, help-seeking behaviours and attitudes, health literacy, self-efficacy and empowerment. Both study arms will be receiving and completing the exact same set of 6-month survey questionnaires prior to the usability assessments. Therefore, the extra step of usability testing done subsequently with the intervention arm only, should not influence or confound the results.

This study is an innovative randomized control trial, in its testing of a youth-driven mHealth intervention for its effectiveness. The study will extend and advance our understanding of whether mHealth interventions can help bridge the health literacy gap, facilitate increased self-efficacy and lead to appropriate help-seeking for the target population.

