### **Analysis**

#### **Power Analysis**

The outcome considered for our power calculation is the average of the GHSQ scale for the formal sources, although similar effect and sample sizes are expected for the informal sources. To determine the sample size required to test the primary hypothesis that the Thought Spot intervention will cause a greater change in help-seeking intentions than usual care, a series of Monte Carlo simulations were

carried out (with 10,000 replications under each test scenario) using SAS System 9.4 for Windows [35]. These simulations assume that the primary hypothesis will be tested using mixed-effect models to account for the longitudinal design, and linear contrasts between time and arm to compare the changes from baseline in both arms. We assume that the test will be 2 tailed and with a critical Cronbach alpha level of 0.05. In order to simulate the data, the means, standard deviations, and within-subject associations are assumed to follow published data that have used similar study designs [36,37]. Based on previous research using the GHSQ [38], a small effect size, equivalent to a Cohen's d of 0.25, was considered (ie, an average change in the GHSQ of 0.41, which is equivalent to a change of 15%), within-subject correlation of 0.6, attrition rate of 40%, and power of 80%. Based on these simulations and specifications, a sample of 236 subjects per arm at baseline is required, which amounts to 472 subjects in total. If 40% attrition is applied to this initial sample, we will be left with 142 subjects per arm (283 in total) after 6 months, at the conclusion of the study.

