## Statistical Analysis Plan Change Log

The following clarifications and analysis were made to the Statistical Analysis Plan listed in the preceding protocol and the published protocol paper published (1).

- In addition to the listed primary outcome of formal help-seeking scores as measured by the GHSQ (Page 17), we conducted an analysis of the help-seeking scores from informal sources as measured by the GHSQ as part of secondary analyses.
- Help-seeking behavior, as measured by the AHSQ, is separated into formal and informal sources, and was analyzed separately as part of secondary analyses.
- In the Power Calculation, a minor correction is made. “Cronbach alpha level of 0.05” actually means “Significance Level 0.05”
- Clarification is made to ‘Linear Contrast’ in the Power Calculation section. The linear contrast mentioned here refers to the difference in change from baseline to the end of the trial. This is the same as our primary test for the efficacy of our outcome
- In our analysis, there was consensus with the research team and literature that gender can affect help-seeking abilities (2, 3). As such, we controlled for gender across all analysis. This may explain part of the variance in the outcome, increasing power. Controlling for gender was not relevant for the conclusions we present as they were the same when not controlling for gender (results not shown).
- To ensure our results are robust, we conducted model diagnostics analysis which includes autoregressive covariance structure instead and in addition to random effect, looking at residuals, Cook’s Distance, Leverage and DFBetas statistics to access outliers, atypical and influential points. Several large values were identified and removal of these values had no impact on our conclusion and no meaningful change in model coefficients. We also inspected the data visually for outliers and normality through the liberal use of graphs.

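### The primary mixed model gives each arm its own baseline mean; a common baseline would cut the variance of the same contrast by 13–14% at the plan's own inputs

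*Protocol*

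**What the plan says.** The Statistical Analysis Plan section makes the formal help-seeking score the dependent variable, with study group and time point as predictors. It adds: "The interaction between study group and time will be included in the model, and linear contrasts will be used to compare the groups", directed at change from baseline to the last visit. The Statistical Analysis Plan Change Log confirms this: "The linear contrast mentioned here refers to the difference in change from baseline to the end of the trial", and says that it is also the primary efficacy test. The baseline GHSQ score is therefore one of the outcome rows, and each arm has a free baseline mean.

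The other terms are "relevant socio-demographics collected at baseline as covariates to control for possible confounding", with gender named in the Change Log. No section states a common baseline mean or adjusts for baseline GHSQ. The Methodology section itself says that randomisation should leave no baseline differences between the groups.

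On timing, Scales/Measures places the socio-demographic form and the GAIN-SS before randomisation. It lists the GHSQ only as given at baseline, 3 and 6 months.

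**The concern.** In a randomised trial the two arms have the same expected baseline score. A model that estimates two baseline means and tests a difference in change subtracts a chance baseline difference more fully than the correlation between visits justifies. At a correlation below 1 this adds variance and removes no bias. Socio-demographic covariates entered as main effects do little about it, because they largely cancel out of a within-person change.

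What is at stake is the width of the primary confidence interval and the power of the primary test. The validity of the test is not in question.

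**Working it through.** **Inputs from the protocol.**
- Allocation (Study Summary): "236 subjects will be recruited for the intervention arm and 236 subjects for the control arm".
- Effect (Power Analysis): "equivalent to a Cohen's d of 0.25", given as 0.41 GHSQ points, so the implied SD is 0.41/0.25 = 1.64.
- Correlation, attrition and power (Power Analysis): "within-subject correlation of 0.6, attrition rate of 40%, and power of 80" per cent.
- Test: two-sided 0.05. The Change Log corrects the reference to Cronbach's alpha to mean the significance level.

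**Assumed, because not given.** Equal SD at every visit, compound symmetry, visits as categories, monotone dropout, and 3-month retention between 60% and 100%.

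**The plan's own figure.** A completers-only change score has SD √(2(1 − 0.6)) = 0.894 in SD units. It needs 201 completers per arm, or 201/0.6 = 335 at baseline. The planned mixed model, which also uses the dropouts' data, needs 294–309 per arm. The stated 236 is not reproduced under these assumptions. The simulation's SDs, correlation pattern and dropout timing are not shown, so this does not prove an error.

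**Two-visit closed form.** With N = 236 randomised and n = 0.6 × 236 = 141.6 completers per arm, the contrast variance in SD units is:
- Separate baselines: 2[(1 − ρ²)/n + (1 − ρ)²/N] = 2[0.64/141.6 + 0.16/236] = 0.01040.
- Common baseline: 2(1 − ρ²)/n = 2 × 0.64/141.6 = 0.00904.

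The ratio is 0.870, a reduction of 13%.

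**Three visits.** The variance comes from the generalised least squares information matrix, summed over the dropout patterns. Power is Φ(0.25/√V − 1.96).

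| 3-month retention | V, separate | V, common | Reduction | Power, separate | Power, common | N per arm for 80%, separate / common |
|---|---|---|---|---|---|---|
| 60% | 0.01040 | 0.00904 | 13.1% | 68.9% | 74.8% | 309 / 268 |
| 80% | 0.01008 | 0.00872 | 13.5% | 70.2% | 76.3% | 299 / 259 |
| 100% | 0.00989 | 0.00853 | 13.8% | 71.0% | 77.2% | 294 / 253 |

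For the 80% row, N = 236 × V × ((1.96 + 0.8416)/0.25)². The standard error in GHSQ points is 1.64 × √0.01008 = 0.165 against 1.64 × √0.00872 = 0.153, about 7% smaller.

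**Sensitivity to the correlation (80% retention at 3 months).**

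| ρ | Variance reduction | Power, separate → common |
|---|---|---|
| 0.3 | 25% | 49% → 60% |
| 0.5 | 17% | 61% → 69% |
| 0.6 | 13% | 70% → 76% |
| 0.7 | 10% | 81% → 85% |
| 0.8 | 7% | 94% → 95% |

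With an autoregressive pattern whose baseline-to-6-month correlation is 0.6, the reduction is 14% and power goes from 72.5% to 78.9%. With no attrition and compound symmetry, the reduction is 20%.

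**The case against.** The strongest reply is that nothing here is wrong. The hypothesis, the simulated contrast and the primary test agree with each other, and the planned contrast is a standard analysis that keeps its type I error. That stands: this is an efficiency point. It is still worth making, because the common baseline targets the same effect with the same data and gained precision in every scenario tried.

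Three stronger readings are tempting, and the documents do not support them.

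- **That the trial is below its stated power.** The simulation inputs are not shown. At a correlation of 0.7 the planned contrast already has 80–82% power with 236 per arm.
- **That the planned model wastes all the baseline information.** Maximum likelihood already uses the baseline rows, including those of dropouts. A completers-only change score has variance 2 × 0.8/141.6 = 0.0113. With 60% retention at 3 months the planned model reaches 0.0104 and the common baseline 0.0090, so the plan already captures (0.01130 − 0.01040)/(0.01130 − 0.00904) = 40% of that gap. With 100% retention it captures 51%.
- **That the primary result should be replaced.** The Change Log reports that the primary analysis was run and gave no evidence of an effect. Moving to a more powerful test after that would be a post hoc change.

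The objection about timing also stands. A common mean is justified only if the GHSQ is completed before allocation is known. The protocol describes blinding of the staff who administer the surveys, not of participants. A self-reported baseline taken after allocation is known could differ between arms, and the constraint could then bias the contrast.

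**Conclusion.** The point holds as a moderate loss of precision in a valid analysis. At the plan's own 236 per arm, 40% attrition and correlation of 0.6, separate baseline means leave the contrast variance 13–14% higher than it could be brought down to. Removing that excess is worth about 6 points of power at d = 0.25, or about 15% more participants (299/259 = 1.15). The size rests on assumed compound symmetry and equal SDs. It shrinks to about 7% at a correlation of 0.8 and grows to about 25% at 0.3. The conclusion depends on baseline GHSQ being collected before allocation is known, which the protocol does not state. It implies neither that the reported primary result is invalid nor that the trial was underpowered.

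**What to change.** 1. State in Scales/Measures whether the baseline GHSQ, and each other repeated scale, is completed before randomisation or at least before the participant knows the allocation. If this cannot be confirmed, keep the change contrast as it is.
2. If it is confirmed, refit the same PROC MIXED model with one baseline mean for both arms: no arm effect at baseline, arm-by-time terms at 3 and 6 months only, and the 6-month arm difference as the contrast. Keep participants who have baseline data only. Using baseline GHSQ as a covariate for the 3- and 6-month scores is an alternative, but it drops participants with no follow-up score.
3. Use the same form for the other continuous scales. The binary AHSQ analysis is not affected.
4. Report the fit as a supplementary analysis, labelled as added after the primary result was known, beside the planned result. After a null finding, an interval about 7% narrower shows better whether the planned 0.41-point effect is excluded.

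The cost is one model statement, a sentence on timing and a short addition to the Change Log. No new data are needed and the estimand is unchanged. In a plan not yet executed, the same model could simply be specified as primary.

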## **Methodology**

This is a partially blind study. The process of inviting students and collecting the data will not be done by the researchers who will have contact with students. Missing values will be minimized by reminders sent to participant at least 3 times and the offer of a reward at the end of the 3rd survey. In the invitation stage we will mention the support of the universities, discuss confidentiality, and explain the importance of the research to foster participation and minimize dropouts. We cannot guarantee that control subjects will not interact with intervention subjects causing some contamination, but given the personal nature of mental health conditions we believe this threat will not be highly prevalent. At the analysis stage we will handle missing values with maximum likelihood estimation, which does not disregard dropouts and is unbiased under MAR (Missing at Random) assumption. Demographic variables (e.g., age, gender, academic year) will be included as covariates which should address differences between groups at baseline and improve estimates, even though these differences are not expected due to the randomization.

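### The protocol's maximum-likelihood, MAR-valid handling of missing data does not extend to the AHSQ, which is assigned to GEE with no weighting, imputation or working correlation named

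*Protocol*

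**What the plan says.** Three statements in the protocol bear on this.

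- Methodology: "we will handle missing values with maximum likelihood estimation, which does not disregard dropouts and is unbiased under MAR (Missing at Random) assumption". The sentence is about the study as a whole and names no outcome.
- Statistical Analysis Plan, in the paragraph on the primary model: "Missing values will be treated with maximum likelihood estimation in SAS PROC MIXED, which uses all available information in the data". Similar models are planned for the other scales.
- Statistical Analysis Plan, closing sentence: "Generalized estimating equations will be used for the AHSQ, since this scale is binary". Nothing is said about weights, imputation, working correlation or the missing-data assumption.

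Help-seeking behaviour is a secondary outcome (Study Summary). The Statistical Analysis Plan Change Log splits the AHSQ into formal and informal sources and calls the secondary analyses exploratory. It also reports an extra sensitivity analysis that added baseline predictors of dropout to make MAR more plausible, and says that this was done for the primary outcome only.

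**The concern.** The protocol claims a property for all its missing-data handling that one of its named analyses does not have. A binary scale explains a logit link. It does not explain giving up MAR validity, because weighted GEE, imputation before GEE and likelihood-based models all exist for repeated binary data.

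The AHSQ is collected at baseline, 3 and 6 months. Whether a student has sought help by one visit could plausibly affect whether that student answers the next survey, and this could differ by arm because only one arm has the app. If so, those still observed at 6 months are a selected group. Unweighted GEE may then report a difference in help-seeking behaviour that is not there, or shrink one that is. The AHSQ is the scale that records actual help-seeking. No planned or reported sensitivity analysis addresses MAR for it: the planned one is a completers-only fit of the primary model.

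**Working it through.** **Figure in the plan.** Power Analysis: "If 40% attrition is applied to this initial sample, we will be left with 142 subjects per arm (283 in total) after 6 months". Check: 236 × (1 − 0.40) = 141.6 per arm and 472 × 0.60 = 283.2 in total, so it reproduces.

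**Assumed inputs.** The documents give no AHSQ rate, correlation or dropout mechanism. Assumed here: 35% seeking help at every visit in both arms, within-person binary correlation about 0.15 to 0.6, 60% retained at 6 months, and dropout odds that depend on the last observed AHSQ value with odds ratio 1, 2 or 3.

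**Target.** The protocol's contrast is arm by change from baseline to 6 months. For a binary outcome this is the ratio of odds ratios (ROR): [odds at 6 months ÷ odds at baseline, intervention] ÷ [the same, control]. With a saturated arm-by-time model and independence working correlation, GEE simply returns the observed proportion at each visit. If baseline is complete and equal by arm, the ROR is the odds ratio of the observed 6-month proportions.

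**By hand, one case.** Latent normal correlation 0.8 between visits, true 6-month rate 0.35 in both arms.

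- Intervention arm, dropout odds 3 times higher after a yes: observed rate 0.283.
- Control arm, dropout unrelated to answers: observed rate 0.350. ROR = (0.283/0.717) ÷ (0.350/0.650) = 0.73.
- Control arm with the opposite mechanism (odds ratio 1/3): observed rate 0.409. ROR = (0.283/0.717) ÷ (0.409/0.591) = 0.57.

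**Direction.** If those who sought help stay more often, the sign reverses. Take latent correlation 0.6 and intervention-arm dropout after 3 months of 50% of non-seekers and 21.5% of seekers. Retention is 0.785 × 0.35 + 0.50 × 0.65 = 0.600, and the observed 6-month rate is 0.393. With control at 0.350, the 6-month odds ratio is (0.393/0.607) ÷ (0.350/0.650) = 1.20 under independence. With exchangeable correlation it was about 0.97, with simulation error about 0.025.

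**Trial-sized simulation.** 236 per arm, 1,500 replicates, latent correlation 0.8, true ROR 1.00, nominal two-sided 5% test with robust standard errors:

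| Dropout | Independence: ROR, rejection | Exchangeable: ROR, rejection |
|---|---|---|
| Unrelated to answers | 1.007, 4.9% | 1.004, 5.1% |
| Same in both arms, OR 3 | 1.002, 5.1% | 1.001, 5.7% |
| Intervention arm only, OR 3 | 0.737, 22.7% | 0.977, 5.4% |
| Opposite by arm, OR 2 | 0.695, 32.1% | 0.999, 5.3% |
| Opposite by arm, OR 3 | 0.560, 67.0% | 0.982, 5.9% |

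**Large-sample simulation.** 400,000 to 1,000,000 per arm, including serially correlated data, true ROR 1.00:

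- Independence: 0.73 to 0.89 with response-dependent dropout in one arm, 0.57 to 0.86 with opposite mechanisms.
- Exchangeable or unstructured: 0.96 to 1.03 throughout.
- Inverse-probability-weighted GEE: 0.99 to 1.00 under arm-dependent MAR dropout.

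With a true ROR of 1.52 and dropout OR 3 in the intervention arm only, independence gave 1.14, exchangeable 1.49 and weighted 1.53.

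**The case against.** The strongest reply is that the protocol never says the GEE is unweighted. It leaves the type of GEE and the working correlation open, and such detail for a secondary outcome is often left to a separate analysis plan. The analysis section also ties maximum likelihood to PROC MIXED and gives the AHSQ its own method, so the Methodology sentence can be read as a loose summary. This has some force. It makes the conflict one of scope, curable by a phrase. It does not remove it, because as written the general promise covers an analysis that cannot keep it by maximum likelihood, and nothing else is named in its place.

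The reply on size also stands in part. Material bias needed two things together: response-dependent dropout that differs by arm, and an independence working correlation. With the same mechanism in both arms and no true effect there was no bias beyond simulation noise.

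A reader might infer more than the documents support:

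- That GEE is valid only under MCAR. It is also consistent when dropout depends only on covariates in the model, and the plan's models include arm, time and baseline socio-demographics.
- That a 20% bias in the odds ratio is to be expected. The 1.20 is a 6-month odds ratio under strong dropout dependence in one arm (a dropout odds ratio of about 3.65) and independence correlation.
- That the GHSQ analysis is safe by contrast. If dropout depends on the AHSQ, that variable is not in the GHSQ model, so its MAR protection needs an assumption of its own.

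**Conclusion.** The point holds in a limited form. The Methodology sentence and the AHSQ method do not agree, and GEE without weighting or imputation is not generally valid under MAR. The possible bias runs from nil to large (ROR about 0.57 to 0.89 for a truth of 1.00), depending on a working correlation that the plan does not state and a dropout mechanism that nobody can know in advance. With exchangeable or unstructured correlation it was about 4% or less in the scenarios tried.

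These sizes rest on assumed rates, correlations and dropout mechanisms, and the 40% attrition is itself a planning assumption. The AHSQ is secondary and exploratory, and the primary GHSQ result is not affected by this choice. The change is worth making because it is cheap and removes a possible bias from the behaviour result. It is not a threat to the trial's main conclusion.

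**What to change.** 1. In Methodology, limit the maximum-likelihood and MAR sentence to the outcomes analysed by mixed models.
2. For the formal and the informal AHSQ, name one MAR-valid method. Either multiply impute missing AHSQ by arm from earlier AHSQ, GHSQ and baseline covariates before fitting the GEE, or use inverse-probability-weighted GEE with the same predictors in the model for remaining in the study. Both keep the marginal odds ratio.
3. Pre-state the working correlation. Where an unweighted GEE is fitted to the imputed data, it should not be independence.

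The change log already reports analyses as done, so where this is run now it should be labelled as added after the fact. The cost is a few lines of code and of plan wording, a little more analysis work, and a small loss of precision from weighting or imputation.
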